### Study objectives

The primary objective of this study is:
Measure the change in HIV-1 incidence following implementation of the DREAMS suite of interventions within a ‘real world, non-trial setting’.

The secondary objectives are to:
Measure HIV prevalence, and proportion of HIV positive AGYW on ART and ART naïve with detectable and undetectable HIV-1 Ribonucleic Acid (RNA) viral load.Measure prevalence of pregnancies and sexually transmitted infections (STIs) including Hepatitis B virus (HBV), Herpes simplex virus type 2 (HSV-2), syphilis, human papillomavirus (HPV*), Chlamydia trachomatis*, *Neisseriae gonorrhoea*, *Trichomonas vaginalis* and *Mycloplasma genitalium.*Measure risky sexual behaviour, specifically, the number of past year sexual partners, condom use, and age-disparate and concurrent partnering.Measure the prevalence of intimate partner violence.Measure performance on selected academic milestones (e.g. academic progress, school completion rates).Measure the economic empowerment of AGYW, socio-economic status of their family and selected parent/guardian/caregiver indicators.To measure the exposure to the DREAMS programme including condom promotion and provision (male and female); HIV testing services (HTS) and linkage to care; GBV prevention and post violence care and support; comprehensive sexual reproductive health rights (SRHR) services; social asset building interventions; school-based HIV and violence prevention; community mobilization and norms change; parenting/caregiver programmes.

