### Data collection

Each participant is assigned a unique study number linked to the questionnaire and administered by study staff using a personal digital assistant (PDA). Study staff with training in phlebotomy will collect two micro-containers of whole blood for DBS and plasma specimens, whilst participants will be guided to collect a VVSS. Blood will be drawn from finger pricks, considered relatively non-invasive and not expected to negatively affect participation. Blood specimens will be stored in sterile containers and logged onto a laboratory tracking sheet. The specimens will then be couriered to a laboratory in KZN for testing. The blood is shipped daily from the study sites to the laboratory. The Standard Operating Procedure for taking blood is based on the protocols of the South African National Department of Health (NDoH) for taking blood for the HIV Polymerase chain reaction (PCR) test [45].

Study staff will administer a questionnaire to obtain:
Socio-economic status of the household, including income, food security and location (urban or rural) and proximity to national roads, clinics and schools.Demographic information of study participants including age, gender, marital status, occupation, employment and educational status.Psycho-social information, including HIV knowledge, attitudes, perceived risk, self-efficacy and social norms related to HIV and AIDS, as well as depression indicators.Academic milestones of study participants, including academic progress and school completion.Behavioural information including age of sex initiation, partner characteristics (including age; number; type (regular/casual); circumcision status, HIV status); partner concurrency; condom use; engagement in transactional sex, substance (including alcohol) abuse and prevalence of intimate partner violence will be collected.Health seeking behaviour, including HIV testing (date of last HIV test, HIV test results) and HIV treatment (initiation date); STIs testing and treatment and contraceptive use.Exposure and engagement with DREAMS interventions.

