### Analysis of secondary objectives

**Measure HIV prevalence, and proportion on ART and ART naïve with detectable and undetectable HIV-1 viral load**: HIV prevalence will be expressed as the proportion testing HIV positive, where the denominator is all who provided a blood sample for HIV testing and had a conclusive result. The proportion of HIV positive AGYW on ART and those not on ART who have detectable or undetectable viral loads will be determined through laboratory tests that have a dynamic range of 20 to 10 million copies/ml. HIV-1 viral load data and Antiretroviral (ARV) drug measurement data will be used to determine the proportion of HIV infected persons on ART and ART naïve with detectable and undetectable viral loads. Participants who achieve viral suppression will be defined as those with a viral load < 1000 copies/ml. Estimated prevalence will take the survey design and sampling weights into account.

**Measure prevalence of pregnancies and sexually transmitted infections (STIs)**: Pregnancy and STIs (overall and individual diseases: (HBV, HSV-2, Syphilis, HPV, *C.trachomatis, N. gonorrhoea, T. vaginalis* and *M. genitalium*) will be calculated with 95% Confidence Interval (CIs). Pregnancy prevalence is defined as the proportion of AGYW testing positive for pregnancy from their blood samples, where all AGYW tested for pregnancy in this study is the denominator. Individual STI prevalence is calculated as the number of individuals testing positive for a particular STI, divided by all AGYW who were tested for STIs. Secondary analysis will be disaggregated by age, gender, marital status, occupation, employment status and educational attainment as well as other socioeconomic indicators and exposure to DREAMS interventions. All estimates will take the survey design and sampling weights into account.

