**To measure the exposure to the DREAMS programme including condom promotion and provision (male and female); HTS and linkage to care; GBV prevention and post violence care and support; comprehensive sexual reproductive health rights (SRHR) services; social asset building interventions; school-based HIV and violence prevention; community mobilization and changes in social norms; parenting/caregiver programmes:** Composite scores will be created for AGYW and caregivers using self-reported data on their exposure to DREAMS activities. The mean score between AGYW exposed to DREAMS interventions and those who haven’t, will be compared using linear regression and by taking the survey design and sampling weights into account.

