The approach of a population-based, cross-sectional survey to evaluate changes in HIV incidence post the DREAMS intervention implementation may limit the attribution of changes in HIV incidence to any specific programme intervention or combination of these. This evaluation will however, provide a reliable picture of HIV incidence amongst AGYW within the DREAMS targeted districts.

Data on intervention exposure, sexual behaviours, number of sexual partners and other sensitive issues will be self-reported and are thus subject to potential recall bias and social desirability bias. To limit the extent of the bias, field staff will be extensively trained on how to gain participant trust, manage sensitive information and assure confidentiality. In order to minimise familiarity, potentially leading to biased responses, fieldworkers will not be assigned to work in their own community.

The results of this study are expected to stand in contrast to findings from randomised controlled trials (RCTs). It is recognized that conclusions drawn from RCTs are not always useful in aiding health programme planning as they are applied to idealized environments, and are only able to measure efficacy in limited populations and fail to identify the complex environmental and community interactions within a study context [49, 50]. In contrast, non-trial data could provide valuable additional insights into the epidemiology of HIV within a real-world setting. Assessing the value of HIV interventions targeting AGYW, requires an evaluation of their impact within the current realities of this vulnerable population [51].

In summary, the highest HIV incidence rates in SA are amongst AGYW. DREAMS is a bold response to this high and sustained HIV-incidence among AGYW, with selected prevention interventions targeting this high-risk population with the aim of reducing HIV incidence by 40%. This study will measure the impact the implementation of DREAMS interventions have had on HIV incidence rates amongst AGYW and examine the factors that contribute to these changes amongst this population within selected districts in South Africa.

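### The planned exposure regression compares a DREAMS exposure score between DREAMS-exposed and unexposed AGYW, so it sets exposure against itself and adds nothing to the objective of measuring exposure

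*Protocol article*

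**What the plan says.** The objective is descriptive. In Study objectives it begins "To measure the exposure to the DREAMS programme including condom promotion and provision (male and female" and goes on to list the other programme components; no outcome is attached to it.

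The last paragraph of Analysis of secondary objectives gives the method in two steps. First, "Composite scores will be created for AGYW and caregivers using self-reported data on their exposure to DREAMS activities". Second, "The mean score between AGYW exposed to DREAMS interventions and those who haven’t, will be compared using linear regression", taking account of the survey design and weights. The exposure score is the only score that this paragraph defines.

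The source of the exposure data is stated elsewhere. Data collection lists "Exposure and engagement with DREAMS interventions" as one questionnaire domain, and the Discussion says "Data on intervention exposure, sexual behaviours, number of sexual partners and other sensitive issues will be self-reported". The Discussion also says that participants come only from DREAMS-targeted areas and that there is no non-DREAMS comparison arm.

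Earlier paragraphs of Analysis of secondary objectives do set outcomes against exposure. The pregnancy and STI results are to be broken down by several characteristics, "as well as other socioeconomic indicators and exposure to DREAMS interventions". The paragraph on behaviour, gender norms, IPV and academic indicators plans the same kind of breakdown.

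**The concern.** A regression is informative when the dependent variable could, in principle, be unrelated to the predictor. Here the dependent variable is how much DREAMS exposure a participant reports, and the predictor is whether she is exposed to DREAMS. If both come from the same answers, the difference in means is positive before any data are seen.

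Two things are at stake. The stated objective gains nothing from the test, since it needs coverage and score estimates with their precision. And a highly significant exposed-versus-unexposed result in the final report could be misread as evidence that the programme worked. That risk matters because the study has no control arm and takes its baseline incidence from other studies, so differences in exposure among participants are an important internal source of evidence on DREAMS.

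**Working it through.** The article gives no figure for this analysis, so there is nothing to reproduce. The check is one of logic, with an illustration.

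**1. Can exposed be defined independently of the score?**
- By self-report: this is the stated source (Data collection; Discussion), and it is also the source of the score.
- By geography: no, because all participants come from DREAMS-targeted areas.
- By programme records: none is described as a source of individual exposure.

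On the text, both sides of the regression therefore rest on the same self-report.

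**2. What follows algebraically?** Assume the score S is a count over the 8 activity groups listed in the exposure paragraph, and that exposed means S ≥ c.
- If c = 1 (any reported activity), the unexposed mean is exactly 0.
- For a higher cut-off, the exposed mean is at least c and the unexposed mean at most c − 1, so the difference is at least 1 whatever the data.

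**3. Size of the built-in difference.** Assume c = 1 and independent uptake p in each group. The exposed mean is then 8p / [1 − (1 − p)^8]. The values of p are assumptions; the article gives none.

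| p | 8p | 1 − (1 − p)^8 | Exposed mean | Unexposed mean |
|---|---|---|---|---|
| 0.02 | 0.16 | 0.149 | 1.07 | 0 |
| 0.10 | 0.80 | 0.570 | 1.40 | 0 |
| 0.30 | 2.40 | 0.942 | 2.55 | 0 |

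**4. Illustrative simulation.** The same three uptakes were used with 300 replicates each and an unweighted, unclustered two-sided 5% z-test. A separate outcome was generated independently of exposure.

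| n | p | Score by exposure: rejected | Outcome by exposure: rejected |
|---|---|---|---|
| 200 | 0.02 | 100% | 7.3% |
| 200 | 0.10 | 100% | 4.7% |
| 200 | 0.30 | 100% | 5.3% |
| 18,500 | 0.02 | 100% | 4.0% |
| 18,500 | 0.10 | 100% | 5.0% |
| 18,500 | 0.30 | 100% | 7.0% |

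The last column is compatible with the nominal 5%: the Monte Carlo standard error is √(0.05 × 0.95 / 300) = 1.3 percentage points. The simulation shows what step 2 implies under its assumed definition of exposed. It is not separate evidence about the study.

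**The case against.** The strongest reply has four parts.

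- **The plan does compare outcomes by exposure.** A reader might infer from the exposure paragraph that the study never sets exposure against outcomes. The article does not support that: two earlier paragraphs break down pregnancy, STI, behaviour, gender norms, IPV and academic results by exposure. This stands, and it confines the flaw to one analysis. The breakdowns name no adjusted model, but a protocol article may leave that to the analysis plan. The paragraph on HIV prevalence does not itself mention a breakdown by exposure.
- **The objective is only to measure exposure.** A reader might fault the analysis for not showing a programme effect, but this objective does not ask for one, and the composite score does serve it. This also stands. The fair criticism is that the regression adds nothing to a descriptive objective. Similarly, the closing aim in the Discussion to "examine the factors that contribute to these changes amongst this population within selected districts in South Africa" is general and says nothing about this regression.
- **By definition depends on a definition that is not given.** A score of zero or the minimum in the unexposed group assumes that exposed means any reported activity. If exposed came from a separate question, the difference would not be guaranteed arithmetically. It would still compare two self-reports of the same thing. In addition, a caregiver's own score compared by the AGYW's exposure would not be strictly circular, since two people report. The text does not state that comparison.
- **Another score may have been meant,** such as the gender-norms mean score or the composites from multiple correspondence analysis. That is possible, but the paragraph does not say so.

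Leaving the matter to the analysis plan does not answer the point. The article names the score, the groups and the model, so an analysis plan that follows it runs a circular test.

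**Conclusion.** The point holds for the AGYW comparison in the exposure paragraph. The score and the grouping are the same self-reported construct, the exposed group is higher by construction, and the test adds nothing to the measurement of exposure. Under the assumed any-activity definition and 2% to 30% uptake per activity group, the built-in difference is about 1.1 to 2.5 points on an 8-point count, and rejection is certain for practical purposes at any realistic sample size.

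The conclusion rests on exposed being derived from the same questionnaire answers as the score, which is the only source the article describes. It does not extend to the caregiver score, to the breakdowns of secondary outcomes by exposure, or to the primary incidence estimate. The wording should be corrected, but the main result does not depend on it.

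**What to change.** In the exposure paragraph of Analysis of secondary objectives:

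1. Remove the regression of the exposure score on exposure.
2. Define exposed: which activities, over what period and with what minimum, from which questionnaire items.
3. Report weighted coverage and mean exposure score with 95% CIs, by district and age, separately for AGYW and caregivers.
4. Use the score as the explanatory variable in survey-weighted regressions of the outcomes that are already to be broken down by exposure (pregnancy, STI, behaviour, gender norms, IPV, academic indicators), and of HIV prevalence. Adjust for age, district and the planned socio-economic composite.
5. Label the results as associations. The survey is cross-sectional with no comparison arm, exposure is self-reported, and the Discussion already concedes that causal inference is limited.

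If a different dependent variable was intended, the paragraph should name it.

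The cost is a change of wording and modest extra modelling on data already collected, with no change to sampling, questionnaire or laboratory work. The downside is a larger set of secondary models to specify and report.

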### Ethical considerations

Verbal consent (or assent) will be obtained from the head of the household for the household composition assessments. Consent will be obtained from all individuals 18 years and older and parental or guardian consent and individual assent will be obtained from all individuals who are younger than 18 years of age. Each study participant will be informed about the study and complete a consent form prior to enrolment, in accordance with 21 CFR Part 50 and ICH Good Clinical Practices (GCP) guidelines [48]. All consent forms and data collection instruments will be translated from English into the local languages. Back translations will be completed and reviewed by a bilingual independent source in order to ensure the accuracy of the translated information. Questionnaires will be administered in participants preferred language.

No personal identifiers will be documented on any of the data collection instruments. All participants will be assigned a unique study number (based on the number on the laboratory package). The study number will be linked to the questionnaire administered by study staff using a handheld PDA. Participants are required to provide written informed consent and assent for their biological samples to be stored beyond the conclusion of the study for any outstanding study related procedures, confirmation of results, HIV related testing and potential future testing. If participants do not consent to long-term storage and additional testing, their samples will be destroyed upon conclusion of the study and after completion of all listed protocol testing.

As the survey instrument contains questions on sensitive topics, including sexual behaviour, GBV, HIV status, access to care and treatment for HIV, it is possible that some individuals may experience discomfort during the interview process. Study staff will also be trained to identify and refer any AGYW to appropriate services who may be a victim of violence or a victim of trafficking, sexual abuse or exploitation, including those who self-identify as sex workers or report receiving money in exchange for sex.

As this is an observational study there are no anticipated adverse events. All unanticipated events will be documented and immediately reported to the Principle Investigator. These unanticipated events will be discussed and a verbal and/or written action plan will be devised and implemented within 48 hours of the submitted report. The study team will maintain written documentation on all events, including details of the action plan and event resolution. If necessary, a formal report will be sent to the Biomedical Research Ethics Committee (BREC) and reported to the Centers for Disease Control and Prevention (CDC) on the CDC’s Incident Report Form 1254 [45].

## Discussion

Ending the HIV/AIDS pandemic by 2030 requires the continual monitoring and evaluation of prevention programmes, with the aim of optimising efforts and ensuring the achievement of epidemic control. The monitoring of HIV prevalence is largely done through household surveys in SA [8]. However, key to determining the impact of initiatives targeting high-risk populations, including AGYW, is the collection of detailed data on the HIV response in a real world context, linking the scale-up of prevention efforts to changes in HIV incidence at a population level. This study will determine the impact DREAMS interventions have had on HIV incidence among AGYW in a ‘real world, non-trial setting’. This will be done by measuring HIV transmission within high-prevalence settings and within a high-risk population group, which will provide insights into the impact and efficacy of the DREAMS suite of prevention interventions.

The monitoring of temporal trends of HIV indicators will assist in improving and targeting prevention efforts and planning for health care delivery needs. This evaluation will be useful in implementing broader surveillance strategies and ensure they are supportive of the DREAMS interventions most effective to reduce risky sexual behaviour, increase knowledge of HIV status and subsequent uptake of ART, as well as reduce the prevalence of GBV.

This study has some limitations. Baseline incidence will need to be estimated. A longitudinal study design would have been preferred to establish baseline incidence prior to commencement of the DREAMS interventions and within the DREAMS targeted areas. Furthermore, a cross-sectional study cannot measure changes in behaviour and HIV incidence over time. This study would also not be able to determine the long-term impact of DREAMS being limited to information based on data gathered at a specific point in time. The study will only select participants from DREAMS targeted areas with the change in HIV infection rates estimated following the implementation of DREAMS programmes amongst AGYW through computation of the population’s attributable risk. As there is no non-DREAMS comparison arm in the study design, causal inferences regarding the relative contribution of DREAMS activities to measured reductions in key parameters is limited. The nature of the study did not allow for the establishment of a control group to assess the relative impact of the DREAMS interventions.

The approach of a population-based, cross-sectional survey to evaluate changes in HIV incidence post the DREAMS intervention implementation may limit the attribution of changes in HIV incidence to any specific programme intervention or combination of these. This evaluation will however, provide a reliable picture of HIV incidence amongst AGYW within the DREAMS targeted districts.

Data on intervention exposure, sexual behaviours, number of sexual partners and other sensitive issues will be self-reported and are thus subject to potential recall bias and social desirability bias. To limit the extent of the bias, field staff will be extensively trained on how to gain participant trust, manage sensitive information and assure confidentiality. In order to minimise familiarity, potentially leading to biased responses, fieldworkers will not be assigned to work in their own community.

The results of this study are expected to stand in contrast to findings from randomised controlled trials (RCTs). It is recognized that conclusions drawn from RCTs are not always useful in aiding health programme planning as they are applied to idealized environments, and are only able to measure efficacy in limited populations and fail to identify the complex environmental and community interactions within a study context [49, 50]. In contrast, non-trial data could provide valuable additional insights into the epidemiology of HIV within a real-world setting. Assessing the value of HIV interventions targeting AGYW, requires an evaluation of their impact within the current realities of this vulnerable population [51].

In summary, the highest HIV incidence rates in SA are amongst AGYW. DREAMS is a bold response to this high and sustained HIV-incidence among AGYW, with selected prevention interventions targeting this high-risk population with the aim of reducing HIV incidence by 40%. This study will measure the impact the implementation of DREAMS interventions have had on HIV incidence rates amongst AGYW and examine the factors that contribute to these changes amongst this population within selected districts in South Africa.

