Each DREAMS country has identified context relevant interventions to include as part of an evidence-based approach to HIV prevention. In South Africa, DREAMS interventions are rolling out in five high HIV burden districts, namely: City of Johannesburg, Ekurhuleni, eThekwini, uMgungundlovu and uMkhanyakude. The DREAMS initiative is executed through existing U.S. government funded programme implementers including community, faith-based and non-governmental organizations, referred to as implementing partners, along with South African Government structures operating at the provincial, district, sub-district, metro, ward and village level. DREAMS aims to scale-up impactful and evidence-based interventions targeting AGYW, in an effort to bring the HIV/AIDS epidemic under control.

The DREAMS suite of interventions includes condom promotion and provision, HIV Counselling and Testing (HTS) and linkages to care, pre-exposure prophylaxis (PrEP) (targeting sex workers specifically), GBV prevention as well as post-violence care and support; linkage to sexual reproductive health (SRH) services, comprehensive sexuality education and social asset building. DREAMS initiatives aim to strengthen school-based HIV and GBV prevention efforts, together with strengthening community mobilisation and norm change efforts through parenting and caregiver programmes, social protection initiatives and interventions specifically targeting male sex partners. The age range of participating AGYW varies across these different activities. For example, 10–14 year olds are not included in condom promotion activities, while PrEP is provided to young women aged 20–24 years who engage in sex work [31]. Whilst younger girls together with boys and men are targeted by some of the aforementioned interventions, this study focuses on females aged between 12 and 24 years of age. The evaluation will provide data on the impact of the DREAMS interventions and will inform future development and potential expansion of these interventions targeting adolescent girls and young women.

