### Study aim

The aim of this study is to determine the impact of the DREAMS initiative on HIV incidence amongst a household-based representative sample of AGYW (12–24 years) in four of the five districts in KwaZulu-Natal (KZN) and Gauteng (GP), South Africa. An HIV incidence baseline will be estimated primarily using incidence findings from existing studies. HIV incidence in the South African National HIV Prevalence, Incidence, Behaviour and Communication Survey Study (SABSSM) used a similar incidence bio-marker-based methodology to one adopted for this study. The HIV incidence findings for AGYW 15–24 years at the national level was 2.54% (95% CI 2.04–3.04) in 2012. An earlier longitudinal study on HIV uninfected 14–30 year old women, undertaken between March 2004 and May 2007, revealed that HIV incidence in young girls below the age of 18 years was 4.7 [95% Confidence interval (CI) 1.5–10.9) compared to 6.9 (95% CI 4.8–9.6)/100 women years (wy) in those aged 18 - 30 [32]. The HIV Incidence Provincial Surveillance System (HIPSS) situated in uMgungundlovu, KZN, included two cross-sectional surveys between June 2014 and June 2015 and between July 2015 and July 2016. The HIPSS study population was drawn from uMgungundlovu, the same area for this study. The HIPSS incidence in adolescent girls 15–19 years was 4.63% (95%CI, 3.29–6.52) and 4.00% (95% CI, 2.74–5.85) for women 20–24 years old in the 2014 survey [33].

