### Study design

This study is a single cross-sectional survey targeting 18,500 AGYW, to be conducted in 2017/2018 in four selected districts in South Africa. AGYW between 12 and 24 years will be selected using a stratified cluster-based sampling approach, with districts representing strata and the cluster or primary sampling unit being the small area layers (SALs). SALs were created by merging adjacent Enumeration Areas (EA), which had less than 500 people, to create a spatial area layer that corresponded as closely as possible to the EA layer. The following criteria were used for the establishment of the SALs. EAs were merged if they fell within the same sub-place (a higher order geographic level); EAs were merged if they had the same geographical properties; an EA was merged if its population that resided there was less than 500 people; and lastly, the resulting SALs must have a population total of 500 or more [37].

Stratified sampling was chosen as it reduces sampling error and ensures a greater level of representation when compared to simple random sampling [38]. It also ensures more precise estimates, provided that there is homogeneity within strata and heterogeneity between strata [38]. A questionnaire will be administered and biological samples collected (two micro-containers of blood for dried blood spot (DBS), plasma specimens and self-collected vulvo-vaginal swab samples (VVSS) to test for HIV infection, HIV incidence, STIs as well as pregnancy respectively).

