### Outcomes and analysis

The primary outcome will be HIV incidence. The analysis will determine whether the aim of an HIV-incidence reduction of 40% at 2 years post implementation of the DREAMS programme in a ‘real world, non-trial setting’ was realised.

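### The Discussion derives the change in HIV infection rates from a population attributable risk, which has no pre-programme term and so cannot give a change over time

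*Protocol article*

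**What the plan says.** The primary objective (Study objectives) is to "Measure the change in HIV-1 incidence following implementation of the DREAMS suite of interventions". Under Outcomes and analysis the test is set: "The analysis will determine whether the aim of an HIV-incidence reduction of 40% at 2 years post implementation of the DREAMS programme" was achieved. The design is one survey: "This study is a single cross-sectional survey targeting 18,500 AGYW, to be conducted in 2017/2018 in four selected districts in South Africa".

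Two routes to a change appear.

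- **External baseline.** The Study aim says "An HIV incidence baseline will be estimated primarily using incidence findings from existing studies". The sample size section is consistent with this. It powers a 40% fall from initial rates of 4 per 100 person-years in KwaZulu-Natal and 3 per 100 person-years in Gauteng.
- **Attributable risk.** The limitations paragraph of the Discussion has "the change in HIV infection rates estimated following the implementation of DREAMS programmes amongst AGYW through computation of the" population's attributable risk. Two sentences before, the same paragraph states that "a cross-sectional study cannot measure changes in behaviour and HIV incidence over time".

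The section on analysis of the primary objective names only the recency assay and ties neither route to the change. On exposure, the secondary analysis plans composite scores "using self-reported data on their exposure to DREAMS activities". The Background describes one component as "pre-exposure prophylaxis (PrEP) (targeting sex workers specifically".

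**The concern.** An attributable risk asks how much of the incidence in a population, at one time, goes with an exposure. The primary objective asks how far incidence has moved since before the programme. One survey can address the first question. The second needs an earlier incidence, which the attributable risk does not use.

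The clause in the Discussion is the only place where the article names the calculation that yields the change, so a reader could take it as the primary estimator. The 40% target would then be judged on a quantity that does not measure it. A real fall could be missed, a rise could go unseen, and differences in underlying risk between exposed and unexposed women could be read as a programme effect or as harm.

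**Working it through.** **The plan's own figures.** The article gives no attributable-risk figure, exposure share or relative risk. The nearest stated figures concern incidence and its change.

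- Precision, from the stated coefficient of variation of 12%: KwaZulu-Natal 4 × (1 ± 1.96 × 0.12) = 3.06 to 4.94 (stated 3.1 to 4.9). Gauteng 3 × (1 ± 2 × 0.12) = 2.28 to 3.72 (as stated).
- Power of 80% for a 40% fall between two equal surveys. The mean duration of recent infection is not given. Assuming 118 to 130 days, a design effect of 1 and a two-sided 5% test, power is 78.9% to 82.7% in KwaZulu-Natal and 78.4% to 82.1% in Gauteng.

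The stated power is attainable under those assumptions. It belongs to a comparison of incidence at two times, so the sample size section follows the baseline route, not the attributable-risk route.

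**Form of the measure.** For an exposure meant to protect, the natural form is the prevented fraction. Let p be the share exposed, I_u the incidence in the unexposed and RR_obs the observed exposed-to-unexposed incidence ratio:

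PF = (I_u − I_pop) / I_u = p × (1 − RR_obs)

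The attributable fraction, (I_pop − I_u) / I_pop, uses the same two incidences with the opposite sign. Neither contains a pre-programme incidence.

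**Check 1: no confounding, with a secular trend.** Assume p = 0.40 and a programme rate ratio of 0.60, with a secular factor s that multiplies incidence in exposed and unexposed alike.

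- PF = 0.40 × (1 − 0.60) = 16%. The factor s cancels.
- Before-after change = s × (1 − 0.16) − 1.
- s = 0.6: 0.504 − 1 = −49.6%.
- s = 1.0: 0.840 − 1 = −16.0%.
- s = 1.3: 1.092 − 1 = +9.2%.

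PF equals the fall only when s = 1. At a rate ratio of 0.60, a PF of 40% would also need p = 0.40/0.40 = 1, which leaves no unexposed group from which to compute it.

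**Check 2: exposed women at higher underlying risk, no secular trend.** Let t be the ratio of underlying risk, exposed to unexposed. Then RR_obs = 0.60t, PF = p(1 − 0.60t), and the true fall is 0.40pt / [(1 − p) + pt]. With p = 0.40:

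| t (assumed) | PF | True fall |
|---|---|---|
| 1.00 | 16.0% | 16.0% |
| 1.25 | 10.0% | 18.2% |
| 1.50 | 4.0% | 20.0% |
| 1.67 | 0% | 21.1% |
| 2.00 | −8.0% | 22.9% |

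The zero point is t = 1/0.60 = 1.67 at any exposure share. Values of t below 1 would push PF upward instead.

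**The case against.** **The clause is brief and undefined.** It sits in a limitations paragraph and gives neither the exposure nor the reference group. The planned regression on self-reported exposure compares mean scores and mentions neither incidence nor attributable risk. This stands: the exposed-unexposed contrast is the usual meaning of the term, not a definition in the document. If the authors meant a comparison with the external baseline, attributable risk is the wrong name for it and the same correction applies.

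**The baseline route is already there.** The Study aim, sample size and outcome sections all point to a change from earlier incidence. This also stands. A reader might infer that attributable risk alone will decide the primary objective. The documents do not show that; they show two unreconciled routes that estimate different quantities.

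**The limits are disclosed.** The article admits that it has no comparison arm, limited causal inference and self-reported exposure. It does not say that the named measure answers another question. Nor does the wish to attribute change to the programme rescue it, since a contrast within one survey supplies no change to attribute.

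**Targeting.** A reader might infer that exposed women are bound to start from higher risk, so that the estimate will be null or reversed. The documents do not support this. They state targeting by risk only for PrEP, and PrEP is not among the exposure components listed in the objectives. Post-violence care is merely listed alongside prevention of violence. Most listed components are broad, such as school, community and parenting programmes, and no risk ratio is given for the package.

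**Conclusion.** The point holds as a conflict between a stated estimator and the stated objective. Population attributable risk, on its usual definition, cannot give the change in incidence from one 2017/2018 survey or decide whether 40% was reached, and it does not agree with the baseline route elsewhere in the article. This needs no numerical assumption.

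The sizes are illustrations. With 40% exposed and a rate ratio of 0.60, the measure stays at 16% while the actual change runs from −49.6% to +9.2% for secular factors of 0.6 to 1.3. Bias from targeting is a possibility only: the measure reaches zero at an underlying risk ratio of 1.67 and is negative above it, but the documents size neither that ratio nor the exposure share.

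**What to change.** Delete attributable risk as the estimator of change in the Discussion. State there, and under the primary analysis, that change is the survey incidence relative to the pre-specified external baseline, with the uncertainty of both carried into the interval.

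If an exposed-unexposed contrast is kept, label it a secondary association and not a measure of change. Adjust it only for factors the programme is not meant to alter, such as district, age and household socio-economic status. Sexual behaviour and violence reported after the programme began are things it aims to change, so adjusting for them could remove part of its effect.

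The cost is wording and, if the contrast is kept, one adjusted model on data already planned for collection. The downside is a wider interval for the change. As an illustration for one province, scale the stated 12% coefficient of variation to a 40% lower incidence: 0.12/√0.6 = 0.155. With the baseline treated as known, the 95% factor is exp(1.96 × 0.155) = 1.35 either way. The baselines cited in the Study aim have log standard errors, from ln(upper/lower)/3.92, of 0.102 (national, 2.04 to 3.04) to 0.193 (provincial surveillance, ages 20 to 24, 2.74 to 5.85). Combining these, √(0.155² + 0.102²) = 0.185 gives a factor of 1.44, and √(0.155² + 0.193²) = 0.248 gives 1.63. That loss is the honest price of an estimated baseline. A ratio to baseline still mixes secular trend with programme effect, so the article's caution about causal inference should stay.
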